## Abstract

**Introduction:**

Ileus is a common and distressing condition characterised by gut dysfunction after surgery. While a number of interventions have aimed to curtail its impact on patients and healthcare systems, ileus is still an unmet challenge. Electrical stimulation of the vagus nerve is a promising new treatment due to its role in modulating the neuro-immune axis through a novel anti-inflammatory reflex. The protocol for a feasibility study of non-invasive vagus nerve stimulation (nVNS), and a programme of mechanistic and qualitative studies, is described.

**Methods and analysis:**

This is a participant-blinded, parallel-group, randomised, sham-controlled feasibility trial (IDEAL Stage 2b) of self-administered nVNS. One hundred forty patients planned for elective, minimally invasive, colorectal surgery will be randomised to four schedules of nVNS before and after surgery. Feasibility outcomes include assessments of recruitment and attrition, adequacy of blinding and compliance to the intervention. Clinical outcomes include bowel function and length of hospital stay. A series of mechanistic substudies exploring the impact of nVNS on inflammation and bowel motility will inform the design of the final stimulation schedule. Semistructured interviews with participants will explore experiences and perceptions of the intervention, while interviews with patients who decline participation will explore barriers to recruitment.

**Ethics and dissemination:**

The protocol has been approved by the Tyne and Wear South National Health Service (NHS) Research Ethics Committee (19/NE/0217) on 2 July 2019. Feasibility, mechanistic and qualitative findings will be disseminated to national and international partners through peer-reviewed publications, academic conferences, social media channels and stakeholder engagement activities. The findings will build a case for or against progression to a definitive randomised assessment as well as informing key elements of study design.

**Trial registration number:**

ISRCTN62033341.

Strengths and limitations of this studyFeasibility outcomes will support the development of a definitive, randomised controlled trial, including considerations of recruitment, device compliance and sham blinding.Qualitative outcomes will explore possible barriers to participation and compliance with the self-administered device before and after colorectal surgery.The study will not explore the most appropriate outcome to be used in a definitive randomised controlled trial, but other related work done in parallel will fill this need.

## Introduction

Ileus is a distressing condition that occurs in 10%–20% of patients undergoing major abdominal surgery.^1^ It is characterised by painful abdominal distension, persistent vomiting and delayed bowel function. This usually resolves 2–4 days after surgery, but in some cases, it may persist in excess of 10 days.^2^ The impact of ileus is extensive. For patients, it increases the length of hospital stay and increases the risk of serious postoperative complications such as pneumonia, surgical site infection and venous thromboembolic events.^3^ For hospitals, it is economically burdensome and is associated with an increase of 71% in healthcare costs.^4^ Once considered to be a normal consequence of surgical recovery, the Association of Coloproctology of Great Britain and Ireland now considers ileus to be a research priority.^5^

In the last 20 years, a number of interventions to prevent ileus and its clinical sequelae have been explored.^6^ Strategies to encourage early or sham feeding (chewing gum) have been studied extensively, but evidence for their effectiveness remains contentious.^7 8^ New approaches to perioperative management (such as intravenous lidocaine) have been explored, but uncertainty relating to efficacy, dose and timing persists.^9^ Novel drugs such as mu-opioid receptor antagonists have shown promising results, but economic and regulatory barriers have limited their uptake beyond North America. The consensus of existing literature suggests that minimally invasive surgery and protocol-driven recovery offer the best chances of preventing ileus.^10^ Uncertainty exists over the pathophysiology of ileus, however, which is problematic for designing clinical interventions that are justified by strong scientific evidence.

Stimulation of the vagus nerve may represent a novel and evidence-based approach to reduce ileus after surgery. In preclinical models, electrical stimulation of the vagus nerve accelerates the recovery of gastrointestinal transit. This is facilitated through vagal afferents targeting the hypothalamic–pituitary–adrenal axis and vagal efferents targeting the cholinergic anti-inflammatory pathway, which attenuate inflammatory-mediated gut dysfunction.^11–13^ Early clinical studies have suggested that this is directly translatable to humans undergoing surgery.^14 15^ Challenges exist, however, as to how vagus nerve stimulation can be done safely, how its efficacy can be optimised and how patient acceptability can be ensured. A protocol for a randomised feasibility trial of non-invasive vagus nerve stimulation (nVNS) to reduce ileus, as well as a series of mechanistic and qualitative studies, is described.

## Methods

### Ethics & governance

Ethical approval for the study was obtained from North East—Tyne and Wear South Research Ethics Committee (19/NE/0217) on 2 July 2019. The study was prospectively registered on the ISRCTN registry (http://www.isrctn.com/ISRCTN62033341) on 11 October 2019 prior to the start of recruitment (online supplemental file 1). The study devices will be provided through the manufacturer’s (electroCore) Investigator Initiated Trial Programme. The present manuscript is reported according to the Standard Protocol Items: Recommendations For Interventional Trials 2013 Checklist (online supplemental file 2).^16^

10.1136/bmjopen-2020-046313.supp1Supplementary data

10.1136/bmjopen-2020-046313.supp2Supplementary data

### Aims and objectives

The aim of this study is to determine the feasibility of performing a multicentre, phase III randomised controlled trial (RCT) of nVNS to reduce ileus after colorectal surgery. The following objectives will explore the case for progression to a phase III trial:

To estimate the proportion of patients screened who are eligible for approach.To estimate the number of approached patients who consent to randomisation.To assess the adequacy of participant blinding to the allocated intervention.To assess participant compliance to the intervention schedule.To explore the safety of the intervention schedule.To estimate the rate of missing outcome data, rate of withdrawal and loss to follow-up.

### Study design

This study is a participant-blinded, parallel-group, randomised, sham-controlled feasibility trial (IDEAL Stage 2b) of nVNS to reduce ileus after colorectal surgery (figure 1). One hundred and forty participants will be recruited across two study sites. Participants will be randomised to four arms (1:1:1:1) according to the following stimulation schedules:

Preoperative stimulation and postoperative stimulation.Preoperative sham and postoperative stimulation.Preoperative stimulation and postoperative sham.Preoperative sham and postoperative sham.

**Figure 1 F1:**
[figure not shown]
Study flow chart.

The estimated trial duration is 24 months, and all participants will be followed up for 30 days after the date of surgery.

### Study setting

The intervention will take place within the community (preoperative stimulation) and in hospital (postoperative stimulation). All participants will undergo surgery at one of two large teaching hospitals (St James’s University Hospital, Leeds, and Bradford Royal Infirmary, Bradford). Both provide elective colorectal cancer services including laparoscopic surgery within a programme of enhanced recovery.

### Eligibility criteria

To be considered eligible for the trial, patients must satisfy all of the following inclusion criteria:

Aged ≥18 years.Able to provide written informed consent.Planned to undergo elective, minimally invasive (laparoscopic or robotic) surgery with a planned anastomosis/no routine plans for a diverting stoma, including one of the procedures listed in table 1.

**Table 1 T1:** Eligible procedures

Right-sided resection	Left-sided resection
Ileocolic/caecal resection	Extended left hemicolectomy
Right hemicolectomy	Left hemicolectomy
Extended right hemicolectomy	Sigmoid colectomy
Transverse colectomy	Rectosigmoid colectomy
**Miscellaneous (side grouped accordingly)**	Anterior resection
Other segmental colonic resection	

Presence of any of the following exclusion criteria will preclude participation in the trial:

Severe cardiac disease (myocardial infarction in the last 12 months, heart failure with New York Heart Association Scale ≥3, second-degree or third-degree atrioventricular block, permanent atrial fibrillation/flutter or previous ventricular tachycardia/fibrillation).Seizures or recurrent episodes of syncope (>1) in the last 5 years.Previous transient ischaemic attack or cerebral vascular accident.Previous vagotomy at any anatomical location.Confirmed diagnosis of chronic gastrointestinal inflammatory condition.Confirmed diagnosis of neuroendocrine tumour.Existing gastrointestinal stoma.Implanted electrical stimulator device (such as cardiac pacemaker or defibrillator).Structural abnormality of the neck anatomy that may impact on use of the device.Belonging to a vulnerable population (such as those lacking capacity and prisoners).Pregnant, nursing or thinking of becoming pregnant during the study period.

Participants will not be eligible for entry into other interventional studies that aim to optimise surgical recovery or for which the intervention may impact on bowel function.

### Intervention

nVNS will be self-administered by participants using the gammaCore device (electroCore, New Jersey, USA). This provides a transcutaneous electrical stimulation comprising of 5×5 KHz sine wave complexes delivered over 1 ms and repeated at 25 Hz (maximum voltage: 24 V; maximum output current: 60 mA). The surface landmark of the carotid pulse is used to guide positioning of the device over the cervical vagus nerve. Participants will self-administer the device twice daily for 5 days before and after surgery, with each administration lasting for 2 min on either side of the neck. Participants will be instructed to adjust the stimulation setting to the maximum tolerated level. A sham device identical in appearance will be used as a control. This produces a subtherapeutic stimulation (0.1 Hz biphasic direct current) while providing a perceptible stimulation sensation.

### Study outcome measures

The following outcomes will assess the feasibility of a phase III RCT of nVNS to reduce ileus:

Proportion of eligible patients identified from screening logs.Number of eligible patients randomised (per month) and reasons for approach failure.Adequacy of participant blinding according to a blinding poll (Bang Blinding Index).^17^Compliance to the preoperative and postoperative stimulation schedules according to participant-reported diaries (maximum of 10 stimulations before and after surgery).Incidence of complications and serious complications within 30 days.Proportion of missing clinical outcome data, withdrawals and loss to follow-up.

Progression will be determined using the parameters outlined in table 2. ‘Progress’ outcomes will build a case for progression to a phase III trial. ‘Adjust’ outcomes will build a case for progression after appropriate amendments have been made. ‘Stop’ outcomes will contraindicate a case for progression, unless modifiable barriers are identified and further assessments of feasibility are undertaken. The predominance of such outcomes will be considered by the research team in the decision-making process.

**Table 2 T2:** Progression criteria

Criteria	Stop	Adjust	Progress
Proportion of eligible patients identified from screening logs	<10%	10%–20%	>20%
Number of eligible patients randomised over 24 months (site: SJUH)	≤2 per month	3–4 per month	≥5 per month
Number of eligible patients randomised over 18 months (site: BRI)	<1 per month	1–2 per month	≥3 per month
Adequacy of participant blinding (according to Bang Blinding Index)	Index <−0.5 Or index >0.5	Index −0.2 to −0.5 Or index 0.2–0.5	Index 0 to −0.19 Or index 0–0.19
Average compliance to the study treatment schedule	<10/20 stimulations across 10 days	10–15/20 stimulations across 10 days	≥16/20 stimulations across 10 days
Proportion of missing clinical outcome data	>40%	15%–30%	<15%
Proportion of randomised patients lost to follow-up	>40%	15%–30%	<15%
Incidence of complications or serious complications	>20% increase in complications	5%–20% increase in complications	<5% increase in complications

BRI, Bradford Royal Infirmary; SJUH, St James’s University Hospital.

Clinical data will be collected to explore variability in candidate measures including number of postoperative days to first flatus, first stool, first oral intake, hospital discharge and GI-2 (composite outcome of passage of stool and oral tolerance).^18^

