### Sample size

As a feasibility study, no formal power calculation has been performed. In this four-arm parallel-group design, 35 participants per arm will allow robust estimates of variability in continuous clinical outcomes, and 70 patients randomised to pre-surgery and post-surgery groups will allow robust estimates of recruitment parameters.^19^ The total sample size of 140 allows robust exploration of both clinical and recruitment-related objectives.

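### The two site recruitment thresholds for Progress in Table 2 together need 174 participants, but only 140 are planned, so a trial that recruits fully on schedule can be rated Progress at one site at most

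*Protocol article*

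**What the plan says.** The planned size is stated twice. Under Study design, "One hundred and forty participants will be recruited across two study sites". Under Sample size, "The total sample size of 140 allows robust exploration of both clinical and recruitment-related objectives". On timing, the Study design section says "The estimated trial duration is 24 months", and the section on patient and public involvement allots two years to the recruitment period.

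Table 2 (Study outcome measures) has eight progression criteria. Two concern the number randomised, one for each site:

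- St James's University Hospital (SJUH), "Number of eligible patients randomised over 24 months (site: SJUH"): Stop at 2 or fewer per month, Adjust at 3–4, Progress at 5 or more.
- Bradford Royal Infirmary (BRI), "Number of eligible patients randomised over 18 months (site: BRI"): Stop below 1 per month, Adjust at 1–2, Progress at 3 or more.

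The text before the table says that Adjust outcomes support progression after amendments, and that the research team will consider which outcomes predominate.

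**The concern.** A monthly rate over a fixed window implies a head count. The head counts implied by the two Progress thresholds should be reachable together within the planned sample size, because both sites draw on the same 140 places. They are not.

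The purpose of this trial is to say whether a phase III trial is feasible, and recruitment supplies two of the eight criteria. If the plan is met exactly (140 randomised in 24 months), at least one site must be rated below Progress, whatever the split. That rating would come from the way the thresholds were set and not from any failure to recruit to plan.

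**Working it through.** **Inputs.** Planned total 140, in four arms of 35 (Study design; Sample size). SJUH: 24 months, Progress at 5 or more per month. BRI: 18 months, Progress at 3 or more per month (Table 2).

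**The plan's own figure.** 4 × 35 = 140. This reproduces exactly. The protocol makes no power calculation, so there is nothing further to reproduce.

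**Head count for Progress at both sites.** Threshold × window, summed over sites:

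| Assumption | SJUH | BRI | Total | Excess over 140 |
|---|---|---|---|---|
| As printed | 5 × 24 = 120 | 3 × 18 = 54 | 174 | 34 (24%) |
| Averages rounded up (4.5 counts as 5, 2.5 as 3) | 4.5 × 24 = 108 | 2.5 × 18 = 45 | 153 | 13 |
| One month off each window for the 30-day follow-up | 5 × 23 = 115 | 3 × 17 = 51 | 166 | 26 |

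**What a full 140 can score over the printed windows.**

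- SJUH just at Progress (120) leaves BRI 140 − 120 = 20, and 20/18 = 1.1 per month: Adjust.
- BRI just at Progress (54) leaves SJUH 140 − 54 = 86, and 86/24 = 3.6 per month: below Progress.
- Progress at both would need an SJUH count of at least 120 and at most 86. No split satisfies this.

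The top of the two Adjust bands is 4 × 24 + 2 × 18 = 132. Full recruitment is thus 8 above the highest pair of Adjust ratings and 34 below the lowest pair of Progress ratings.

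**If the rate is taken over months actually open.** At exactly 5 and 3 per month, 140 is reached at 140/8 = 17.5 months if both sites open together. If BRI opens 6 months after SJUH (an assumption suggested by the 24- and 18-month windows), SJUH has 30 by then and 140 is reached at 6 + (140 − 30)/8 = 19.75 months. The counts would be 5 × 19.75 = 98.75 and 3 × 13.75 = 41.25. Per month open, both sites are at Progress. Divided by the printed windows, the same recruitment gives 98.75/24 = 4.1 and 41.25/18 = 2.3 per month, and neither site is at Progress.

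**The case against.** The strongest reply is that the bands are monthly rates, not totals. The outcome list under Study outcome measures also describes the measure as a number per month. If a site that finishes early is judged over the months it was open, both sites can be rated Progress, as the last calculation shows. The 24 months is only an estimate, so finishing early contradicts nothing, and a statistical analysis plan that is not shown could define the denominator.

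Part of this stands. A reader might infer that Progress at both sites can never be reached, or that recruitment must stop at 140. The document supports neither. The impossibility holds for the printed windows, and 140 is the planned total, with no stopping rule stated and no over-recruitment described. But both row labels print a fixed window, and no text sets a shorter one. The reply also helps only a trial that beats its own timetable. One that uses the planned 24 months to reach 140 still cannot be rated Progress at both sites.

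A second reply concerns consequences. A reader might infer that the table would block a phase III trial. It would not: Adjust supports progression after amendments, no single row decides, and even Stop is qualified where barriers can be modified. With 140 randomised, a Stop rating needs an extreme split (48 or fewer at SJUH, or 17 or fewer at BRI), which would be poor recruitment at that site in its own right. The bar may also have been set high on purpose, although the document does not say so.

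Finally, a reader might infer that some splits fall in no band at all, such as SJUH 97–103 with BRI 43–37 (4.04–4.29 and 2.39–2.06 per month). That requires unrounded rates. Rounded to whole numbers, these are 4 and 2, both Adjust, so the point does not rest on it.

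**Conclusion.** The two recruitment rows of Table 2 are inconsistent with the planned sample size. Progress at both sites over the stated windows needs 174 randomised as printed, or 153 under lenient rounding, against 140 planned. A trial that recruits its full 140 on the 24-month schedule can be rated Progress at one site at most, which understates recruitment feasibility.

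This rests on taking the window in each row label as the denominator and 140 as the number recruited. The effect is moderate, since it can pull one or both of eight ratings down but cannot by itself prevent progression. It should still be settled before the recruitment data are rated, because the choice of denominator made afterwards could decide the rating.

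**What to change.** Adopt one of the following before the recruitment data are rated:

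1. Define each site's rate as participants randomised per month that the site was open, up to the 140th randomisation, in place of the fixed 24- and 18-month windows. This keeps the thresholds. Progress at both sites then still requires recruitment faster than the 24-month plan, so the team should confirm that this is intended.
2. Keep the windows and reset the Progress thresholds *a* (SJUH) and *b* (BRI) so that 24*a* + 18*b* is at most 140. Redraw the adjoining bands so that they neither overlap nor leave gaps.
3. Replace the two rows by one combined criterion, with 140 randomised within 24 months rated Progress.

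The cost is rewording two rows of one table. If thresholds are reset, the Progress bar is slightly lower. Trial conduct does not change.

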In contrast, there are several possible challenges associated with studying and implementing nVNS in this setting. First, patient self-administration requires adequate skill, understanding and compliance, which may be difficult in the post-operative setting. A dedicated programme of training, including device positioning, aims to mitigate this. Second, the non-invasive approach to stimulation is less precise than conventional stimulation since contact with the vagus nerve cannot be confirmed objectively. This is mitigated through the use of a standard technique (stimulation over the cervical surface landmark), which has been shown to increase heart rate variability, reduce markers of systemic inflammation and generate vagal somatosensory evoked potentials (indicators of vagal stimulation) previously in healthy volunteers.^31–34^ Finally, identifying an adequate sham intervention by which to compare nVNS is challenging. In previous healthy volunteer studies, nVNS has been shown to significantly reduce the expression of inflammatory cytokines from baseline but not when using the sham device.^32^ It is possible that manual instrumentation of the device may be sufficient to elicit some vagal activity, but this is considered minimal and is comparable across both device types. Providing that these challenges can be addressed, nVNS may provide a practical approach to stimulating the vagus nerve in the pre-operative and post-operative setting.

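### Table 2 grades compliance only as a pooled total out of 20, with no minimum for either phase, so high preoperative use can mask poor postoperative use

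*Protocol article*

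**What the plan says.** All references are to the Protocol article.

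- **Intervention.** "Participants will self-administer the device twice daily for 5 days before and after surgery". 
- **Study setting.** "The intervention will take place within the community (preoperative stimulation) and in hospital (postoperative stimulation").
- **Study outcome measures, outcome list.** The feasibility outcome names both schedules: "Compliance to the preoperative and postoperative stimulation schedules according to participant-reported diaries (maximum of 10 stimulations before and after surgery").
- **Study outcome measures, Table 2.** There is a single row, "Average compliance to the study treatment schedule", with Stop at "<10/20 stimulations across 10 days", Adjust at "10–15/20 stimulations across 10 days" and Progress at "≥16/20 stimulations across 10 days". No row or footnote sets a minimum for either phase.
- **Study outcome measures, text above Table 2.** Adjust supports progression once amendments have been made. Stop argues against progression unless barriers that can be changed are found and feasibility is assessed again. The research team weighs the criteria together.
- **Discussion.** The authors say where they expect trouble: "patient self-administration requires adequate skill, understanding and compliance, which may be difficult in the post-operative setting".

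**The concern.** The outcome has two components, and the progression rule keeps only their sum. The components differ in ways that matter for feasibility: one takes place at home before surgery, the other on a ward during recovery, and the authors single out the second as the difficult one.

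The four arms cross active and sham stimulation before surgery with active and sham stimulation after it, and the mechanistic substudies are meant to inform the final schedule. A phase III trial could therefore use the preoperative schedule, the postoperative schedule or both. That choice needs to know whether each schedule can be delivered, and a verdict on the total does not say. Table 2 already splits recruitment by site with separate thresholds; compliance has no matching split by phase.

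At stake is the progression decision on a stated objective. A weak postoperative schedule can be graded more favourably than it deserves, or a workable preoperative schedule can be marked down for failure in the other phase.

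**Working it through.** **Inputs.** Two stimulations a day for 5 days in each phase (Intervention); a maximum of 10 per phase (outcome list); bands of below 10, 10 to 15, and 16 or more out of 20 (Table 2).

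**The plan's own denominator.** 2 × 5 = 10 per phase, and 10 + 10 = 20 over 10 days. This agrees with Table 2.

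**Assumption.** The average is a mean taken over the same participants in both phases, so the pooled mean is the preoperative mean plus the postoperative mean.

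**What the sum allows.** For a preoperative mean *p*:

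- smallest postoperative mean that avoids Stop = 10 − *p*
- smallest postoperative mean that gives Progress = 16 − *p*

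| Preoperative mean | Avoids Stop from | Gives Progress from |
|---|---|---|
| 10/10 | 0/10 | 6/10 |
| 9/10 | 1/10 | 7/10 |
| 8/10 | 2/10 | 8/10 |
| 7/10 | 3/10 | 9/10 |
| 6/10 | 4/10 | 10/10 |

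**Comparison with the same proportions applied to one phase.** Table 2's cut-points are 10/20 = 50% and 16/20 = 80%, that is 5/10 and 8/10.

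- 10 + 0 = 10: pooled Adjust; postoperative phase alone 0/10, Stop.
- 9 + 1 = 10: pooled Adjust; postoperative phase alone 1/10, Stop.
- 8 + 2 = 10: pooled Adjust; postoperative phase alone 2/10, Stop.
- 10 + 6 = 16: pooled Progress; postoperative phase alone 6/10, Adjust.
- 9 + 7 = 16: pooled Progress; postoperative phase alone 7/10, Adjust.
- 8 + 8 = 16: pooled Progress; postoperative phase alone 8/10, Progress. Here the two agree.

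**How wide the masking is.** Against 5/10, the postoperative shortfall that escapes Stop is 5 − (10 − *p*) = *p* − 5, so it exists whenever *p* exceeds 5 and is at most 5 stimulations. Against 8/10, the shortfall that still reaches Progress is 8 − (16 − *p*) = *p* − 8, so it exists only when *p* exceeds 8 and is at most 2 stimulations.

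**The other direction.** 9 + 0 = 9, which is Stop, although the preoperative schedule alone reached 9/10 = 90%.

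**The case against.** Several points on the other side have force.

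- **The extreme cases are conditional.** A reader might infer that Table 2 always rates complete postoperative failure as Adjust and 60% postoperative compliance as Progress. It does not. Both ratings need a preoperative mean of exactly 10/10, meaning that every participant completes every home stimulation. At 9/10 before surgery, 0/10 after is Stop and 6/10 after gives 15/20, which is Adjust.
- **Adjust is not a pass.** It calls for amendments first. If home use is perfect and hospital use fails, amending the combined schedule is a reasonable response.
- **The information is not lost.** The outcome is defined by phase, compliance is to be presented descriptively with confidence intervals, interviews sample on device compliance, and the team keeps discretion. A reader might infer that Table 2 by itself would carry an unworkable schedule into phase III. The documents do not support that; the team would also have to overlook results by phase that it can see.
- **The total is coherent.** Every arm uses a device in both phases, so 20 stimulations is the burden actually tested. Nothing here contradicts itself; this is a design choice.
- **Separate rows could misgrade too.** If a Stop in the postoperative row blocked progression outright, it would rule out a preoperative-only trial with full compliance. Two rows could also count compliance twice when the criteria are weighed.

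The first four points limit the size of the problem but do not remove it. The team's discretion works across rows and supplies no threshold for a phase hidden inside one row, and a Progress grade on the total prompts no amendment. The last point is answered by the wording of the fix.

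**Conclusion.** The concern holds in a limited form. Table 2 fixes a progression rule on the pooled total and sets no minimum for either phase, although the outcome is defined for both and the authors expect difficulty in one.

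The masking does not depend on perfect home use: any preoperative mean above 5/10 lets some postoperative compliance below 50% avoid Stop, and any above 8/10 lets some below 80% reach Progress. The false-Progress zone is narrow, at most 2 of 10 stimulations; the zone that escapes Stop is wider, up to 5 of 10. The opposite error, a Stop despite 90% preoperative compliance, arises from the same pooling.

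This rests on reading the average as a mean over common participants and on using the plan's own 50% and 80% as the yardstick for a single phase. The documents give no forecast of compliance, so how likely these combinations are is unknown. The randomised data are unaffected; what suffers is the use of the compliance result in the progression decision. The change is worth making because it is cheap and makes the criterion answer the question about the schedule.

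**What to change.** In Table 2, grade preoperative and postoperative compliance separately, each out of 10: Stop below 5, Adjust 5 to below 8, Progress 8 or more. Keep the total out of 20 as a descriptive figure. Add two sentences of interpretation:

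1. The grade for a phase bears on carrying that phase's schedule into phase III, so a Stop in one phase does not by itself rule out a trial of the other phase alone.
2. The two grades count together as one compliance criterion when the team weighs the criteria as a whole.

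**Cost.** Wording in Table 2 and the analysis plan only. The stimulation diaries already cover both phases (Table 3), so no new data are needed. There are two downsides: the postoperative grade may be less favourable than the current total, and the per-phase cut-points are the pooled ones scaled down, not independently justified, which the plan should say.

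### Withdrawal is a stated feasibility objective and outcome, but Table 2 has no progression criterion for it, so the retention row can read Progress however many participants withdraw

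*Protocol article*

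**What the plan says.** The last objective under Aims and objectives is "To estimate the rate of missing outcome data, rate of withdrawal and loss to follow-up". The outcome list under Study outcome measures repeats the three items: "Proportion of missing clinical outcome data, withdrawals and loss to follow-up". In both places withdrawal stands beside loss to follow-up as a different item.

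The same section then says "Progression will be determined using the parameters outlined in table 2". Table 2 has two rows that bear on attrition:

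- "Proportion of missing clinical outcome data", with no denominator named;
- "Proportion of randomised patients lost to follow-up", where the denominator is those randomised.

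Both rows use the same bands: Progress below 15%, Adjust from 15% to 30%, Stop above 40%. There is no row for withdrawal, and nothing in the article says that loss to follow-up includes it.

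On combining the rows, the section says "The predominance of such outcomes will be considered by the research team in the decision-making process".

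**The concern.** A feasibility trial's progression thresholds are useful because they are fixed before the data are seen. Here one of the three attrition measures that the protocol sets out to estimate has no threshold. Read literally, and in line with the protocol's own separation of the terms, a participant who withdraws does not count in the retention row. That row can then look good while a sizeable share of those randomised have left the trial. The decision at stake is whether to go to a phase III trial and what attrition to plan for in it.

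**Working it through.** **Inputs.** Sample size section: 4 arms × 35 = 140, which agrees with the stated total ("The total sample size of 140 allows robust exploration of both clinical and recruitment-related objectives"). Table 2: the bands given above. The article gives no expected withdrawal or loss rates, so the counts below are assumptions chosen for illustration.

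**Step 1: limits of the retention row.** With *l* participants lost, the row reads *l*/140.

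- 20/140 = 14.3%, Progress; 21/140 = 15.0%, Adjust. So up to 20 lost reads Progress.
- The number withdrawn, *w*, does not enter the formula.
- 42/140 = 30.0% is the top of Adjust, and 57/140 = 40.7% is the first count in Stop. Counts from 43 (30.7%) to 56 (40.0%) have no grade.

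**Step 2: compare the row as worded with combined attrition.** Combined attrition is (*w* + *l*)/140. For the missing-data row, suppose that everyone withdrawn or lost has no outcome data and everyone else is complete. The row then reads (*w* + *l*)/140 if all randomised count, or *l*/(140 − *w*) if withdrawn participants are left out.

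| Withdrawn | Lost | Retention row as worded | Combined attrition, and missing data over all 140 | Missing data, withdrawn left out |
|---|---|---|---|---|
| 28 | 10 | 10/140 = 7.1%, Progress | 38/140 = 27.1%, Adjust | 10/112 = 8.9%, Progress |
| 35 | 0 | 0/140 = 0%, Progress | 35/140 = 25.0%, Adjust | 0/105 = 0%, Progress |
| 35 | 14 | 14/140 = 10.0%, Progress | 49/140 = 35.0%, no grade | 14/105 = 13.3%, Progress |
| 57 | 0 | 0/140 = 0%, Progress | 57/140 = 40.7%, Stop | 0/83 = 0%, Progress |

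**Step 3: what the table shows.** In all four cases the retention row reads Progress, while the combined rate on the same bands never does. Whether the missing-data row signals the problem depends entirely on its denominator.

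**The case against.** The strongest reply is that withdrawals do not escape Table 2. The Statistical analysis plan section says that all analyses are done by intention to treat. On the natural reading, a participant who withdraws from data collection is then a randomised participant with missing outcomes, and the missing-data row reads 27.1%, Adjust, in the first case. Much of this stands, and it is the probable reading. It does not settle the matter. The same section also runs every analysis in a per-protocol population, from which any deviation from the stimulation schedule is a possible reason for exclusion. Table 2 does not say which population its rows use, and the missing-data label lacks the denominator that the retention label has.

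The compliance row may also register withdrawals. Suppose 35 participants withdraw after 5 stimulations and 105 complete 18, with all counted. The mean is (35 × 5 + 105 × 18)/140 = 2065/140 = 14.75 of 20, which is below the 16 needed for Progress. That is a fair point, but the row is an average of device use. It does not measure retention, and the article does not say how withdrawn participants enter it.

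Third, Table 2 is not mechanical. The team judges the predominance of outcomes, withdrawals will be reported anyway, and Adjust still supports progression after amendment. This limits the consequence. It does not supply a grade for withdrawal to be weighed.

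Finally, operational definitions may stand in the full protocol or analysis plan, which are not shown. The unstated denominator alone would be no finding for that reason. The point rests on a mismatch within one printed section, between the outcome list and the table that is meant to judge it.

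**Conclusion.** The point holds, with limited weight. Withdrawal is an objective and an outcome without a progression criterion. As worded, the retention row reads Progress with up to 20 of 140 lost, regardless of withdrawals. In the first illustration the gap is 7.1% against 27.1%, one grade apart. This assumes that loss to follow-up excludes withdrawal, as the protocol's two lists imply. The withdrawal counts are illustrative, but the logic does not depend on them.

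Three stronger readings are not supported:

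- A reader might infer that a trial with heavy withdrawal would pass on attrition altogether, or would be graded Progress overall. That requires withdrawn participants to be left out of the missing-data row as well, which the article does not say, and it ignores the team's judgement across rows.
- A reader might infer that withdrawal will be the main form of attrition because the device is self-administered around surgery. The Discussion accepts that compliance may be difficult after surgery, but the article gives no rates for withdrawal or loss.
- A reader might infer that someone who withdraws before surgery has no outcome form due, and so cannot count as missing. Table 3 schedules the forms without such an exemption, and the Study design section plans 30-day follow-up for all participants.

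**What to change.** Four small changes to Table 2:

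1. Reword the retention row as: *Proportion of randomised patients who withdrew from outcome collection or were lost to follow-up by 30 days (denominator: all randomised)*.
2. Score the missing-data row over all randomised participants, and say so in its label.
3. State that participants who only stop using the device but remain in follow-up count under compliance and not under attrition.
4. Assign a grade to the range from 30% to 40%, so that the combined rate is always scored. Without this, 35 withdrawn and 14 lost (35.0%) would have no grade even in the reworded row. The team should confirm at the same time that bands set for loss to follow-up are the ones it wants for the combined rate.

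The cost is a few words in one table. No new data are needed, because withdrawals are already an outcome. The drawback is that the retention figure becomes somewhat less favourable, since it now counts people whom the present row omits.
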